#### Approach for cases of dropout/lost to follow-up/need to screen

1. Dropout cases will be defined as enrolled participants who miss a treatment session or refuse treatment as scheduled. We will consider at least 80% of the planned recruitment (40 cases in each group) to provide sufficient data for analysis.

2. Lost to follow-up will be defined as participants who complete all treatments, but cannot be contacted for follow-up.

3. Need to screen will be defined as enrolled participants who have serious adverse events during the trial. Researchers will be expected to halt treatment immediately and note the reason for the adverse event.

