### Outcome measures

#### Primary outcome

1. Patient adherence: Participant dropout,participants lost to follow-up, and reasons will be recorded (Table 1).

**Table 1 T1:** Schedule for treatment and outcome measurement

**Item**	**Screening**	**Treatment**															**Follow-up**		
**Session**	**1 (baseline)**	**2**	**3**	**4**	**5**	**6**	**7**	**8**	**9**	**10**	**11**	**12**	**13**	**14**	**15**	**16**	**17 (+1 m)**	**18 (+2 m)**	**19 (+3 m)**
Eligibility screening	√																		
Informed consent	√																		
Patient preference screening	√																		
Allocation	√																		
Patient expectation toward treatment	√																		
Treatment		√	√	√	√	√	√	√	√	√	√	√	√	√	√	√			
Widespread pain index	√					√					√					√	√	√	√
Symptom severity	√					√					√					√	√	√	√
Visual analogue score	√					√					√					√	√	√	√
Fibromyalgia intensive questionnaire	√															√	√	√	√
Hamilton depression scale	√															√	√	√	√
SF-36 Health survey	√															√	√	√	√
Patient satisfaction of treatment																√			
Number of dropouts or lost to follow-up																√			√
Practitioner attitude toward research model																√			√
Recording of adverse events	√	√	√	√	√	√	√	√	√	√	√	√	√	√	√	√	√	√	√

2. Patient satisfaction for the treatment: Patient satisfaction will be assessed at week 5 (Table 1). Satisfaction will be measured using a seven-score scale, with 1 for “very satisfied” and 7 for “very dissatisfied”.

3. Practitioner attitude for the research model: Individual or focus group interviews will be conducted after the trial (Table 1). All practitioners in the study (acupuncturists and cupping therapy practitioners) will be interviewed for their disposition toward conducting the PRPP trial model and their thoughts on this model compared with traditional randomized controlled trials.

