#### Secondary outcomes

1. Adverse events: Adverse events will be observed during the five weeks of treatment and three months follow-up (Table 1). Researchers will be expected to note minor and serious adverse events that occur, including case ID number and symptoms.

2. Patient expectation for the treatment: Patient expectation will be assessed at week 0 (Table 1), measured by a four-score scale, with 1 for “symptoms totally disappeared” and 4 for “no change in symptoms”.

3. Visual analogue scale (VAS) [27] for pain intensity: The length of the VAS we will use is 100 mm, with “0” representing no pain and “100” representing unbearable pain that affects appetite and quality of sleep. Researchers will be expected to show the scale to patients and note the pain scores. VAS for pain will be measured once daily during week 0, at the end of every fifth treatment session (for a total of 15 assessments during the five-week treatment period), then during weeks 9, 13, and 17 of the follow-up period (Table 1).

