#### Other outcomes

1. Widespread pain index (WPI) for pain intensity: The WPI is defined based on the ACR diagnostic criteria for fibromyalgia [26]. The WPI will be measured once daily during week 0, at the end of every fifth treatment session (for a total of 15 assessments during the five-week treatment period), then during weeks 9, 13, and 17 of the follow-up period (Table 1).

2. Symptom severity (SS) for pain intensity: SS is defined based on the ACR diagnostic criteria [26] for fibromyalgia. SS will be measured once daily during week 0, at the end of every fifth treatment session (for a total of 15 assessments during the five-week treatment period), then during weeks 9, 13, and 17 of the follow-up period (Table 1).

3. Hamilton Depression Scale (HAMD; Chinese translation) for depression [28]: The HAMD will be implemented three times at weeks 0, 5, and 17 (Table 1).

4. Quality of life measured by the SF-36 Health Survey (Chinese translation) [29]: The SF-36 will be implemented three times, at weeks 0, 5, and 17 (Table 1).

5. Revised Fibromyalgia Impact Questionnaire (FIQR, Chinese translation) for pain intensity [30]: The FIQR will be implemented three times, at weeks 0, 5, and 17 (Table 1).

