#### Statistical analysis

To evaluate the feasibility of the PRPP model, we will use the chi-square, Cochran-Mantel-Haenszel (CMH)-chi-square, or Fisher’s exact test (as appropriate) to compare patient adherence and satisfaction toward treatment between groups and qualitative research methods to analyze patient and practitioner attitudes.

To assess the therapeutic effect of acupuncture and cupping therapy for fibromyalgia, we will use the chi-square, CMH-chi-square, or Fisher’s exact test (as appropriate) to compare baseline characteristics for categorical data. Analysis of variance (normal distribution) or non-parametric tests (skewed distribution) will compare baseline characteristics for continuous data. Analysis of primary outcomes will involve contrast analysis in which cupping therapy will be compared with acupuncture. This will indicate whether or not cupping and acupuncture differ in efficacy. This analysis will be conducted using repeat measurements in which outcomes will be compared at each follow-up, controlling for baseline scores. Intention-to-treat analysis[31] will be used in which missing data will be supplemented using the value that was assessed at the prior session (for example, if participant drops out at treatment session 6, then all outcome data would be noted as values at session 5). All calculations will be performed using SPSS for Windows (version 17.0, Chicago, Illinois), and *P*-values under .05 will be considered significant.

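### Carrying the last value forward as the intention-to-treat method fixes dropouts' pain scores at an early value and assumes no relapse after week 5

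*Protocol article*

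**What the plan says.** The Statistical analysis section of the protocol article plans the efficacy comparison as follows: "This analysis will be conducted using repeat measurements in which outcomes will be compared at each follow-up, controlling for baseline scores". It then fixes how gaps are filled, "missing data will be supplemented using the value that was assessed at the prior session", and illustrates the rule: "if participant drops out at treatment session 6, then all outcome data would be noted as values at session 5". This is last observation carried forward (LOCF), presented as the intention-to-treat analysis.

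The schedule decides what is carried:

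- **VAS.** Table 1 has it at baseline, at columns 6, 11 and 16 (after the fifth, tenth and fifteenth treatments), and "then during weeks 9, 13, and 17 of the follow-up period".
- **HAMD.** "The HAMD will be implemented three times at weeks 0, 5, and 17". The text gives SF-36 and FIQR the same timing. Table 1 also ticks months 1 and 2, but in both places only baseline precedes week 5.
- **Satisfaction**, a primary outcome, is taken once, at week 5 (column 16).

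The section on dropout defines the first group concerned: "Dropout cases will be defined as enrolled participants who miss a treatment session or refuse treatment as scheduled". It defines loss to follow-up as completing treatment and then being unreachable. The sample size section names an equivalence hypothesis for pain and allows for 15% dropout.

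**The concern.** Pain is expected to fall over five weeks of treatment and may return in the twelve weeks after it. LOCF handles neither movement. A treatment-phase dropout keeps baseline or an early VAS value through week 17. For HAMD, SF-36 and FIQR such a dropout is always given baseline. Someone lost after week 5 keeps the end-of-treatment value at weeks 9, 13 and 17.

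The two errors run in opposite directions: the first understates an arm's benefit, the second overstates its durability. If the arms lose different shares, the difference in dropout appears as a difference in efficacy. If they lose equal shares, a real difference is pulled toward zero, which is the direction that favours an equivalence conclusion.

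The worked example is also ambiguous. If sessions are counted by Table 1 columns, session 5 has no VAS and the last value is baseline. If treatments are counted, the fifth treatment is column 6, where VAS is measured.

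**Working it through.** The plan gives no figure for the effect of missing data, so its planning figures are used.

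**Inputs from the sample size section.** VAS change 12.78 mm, SD 5.88 (cupping); effect size 0.2875; 38 per group at 80% power; 15% dropout.

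**Inputs assumed.** The same change in both arms; the dropout splits; dropout unrelated to outcome; the carried change is either zero (baseline) or one third of a linear change (first of three on-treatment assessments).

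**Reading of the effect size.** The type is not stated. Read as Cohen's f in a between-factor repeated-measures ANOVA, λ = N f² m / (1 + (m − 1)ρ). With m = 4 and ρ = 0.7 (both assumed), λ = 76 × 0.2875² × 4 / 3.1 = 8.11, and power is 0.80 at 76 participants. The plan's total is thus recovered under these assumptions. For two groups d = 2f = 0.575, or 0.575 × 5.88 = 3.38 mm.

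**Bias in one arm** = share missing × (true change − carried change).

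- 15% dropout, baseline carried: 0.15 × 12.78 = 1.92 mm understated.
- 15% dropout, one third carried: 0.15 × 2/3 × 12.78 = 1.28 mm understated.
- 15% lost after week 5, full relapse among them: 0.15 × 12.78 = 1.92 mm overstated in follow-up. At 5% and 25% lost: 0.64 and 3.20 mm.

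**False difference between arms when none exists**

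| Dropout | One third carried | Baseline carried |
|---|---|---|
| 10% vs 20% | 0.10 × 2/3 × 12.78 = 0.85 mm | 0.10 × 12.78 = 1.28 mm (0.22 SD) |
| 5% vs 25% | 0.20 × 2/3 × 12.78 = 1.70 mm | 0.20 × 12.78 = 2.56 mm (0.43 SD) |

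**Type I error.** Simulation with 10,000 trials per setting, two-sample t test on change scores, baseline carried. Here 25 per arm is the randomized stratum and 50 per arm is all 100 participants if they split evenly.

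| Dropout | 25 per arm | 50 per arm |
|---|---|---|
| 15% vs 15% | 0.05 | 0.05 |
| 10% vs 20% | 0.10 | 0.14 |
| 5% vs 25% | 0.25 | 0.44 |

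Testing observed values only gave about 0.05 throughout.

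**Equal 15% dropout with a true difference of 3.38 mm.** With baseline carried, the expected difference is 0.85 × 3.38 = 2.87 mm. With 50 per arm, power to detect a difference is 0.56, against 0.74 from observed values only.

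**Equivalence, illustrated with a margin of 3.38 mm.** The plan states no margin. Carrying baseline also widens the spread:

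- Better arm: √(0.85 × 5.88² + 0.85 × 0.15 × 12.78²) = 7.09.
- Other arm (mean 9.40): √(0.85 × 5.88² + 0.85 × 0.15 × 9.40²) = 6.38.
- With 50 per arm, SE = √((7.09² + 6.38²)/50) = 1.35. Equivalence is declared if the estimate lies within 3.38 − 1.66 × 1.35 = 1.14 mm of zero.
- With the estimate centred at 2.87, that probability is about 0.10. Complete data would give 0.05.

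With 25 per arm the wider spread outweighs the shrinkage and the probability falls below 0.05. The net effect therefore depends on the margin and the numbers.

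**The case against.** VAS is a secondary outcome in a trial whose first aim is feasibility, and sensitivity analyses may stand in an analysis plan that is not shown. Both points hold. They limit the weight of the finding, but they do not remove a method that the article itself fixes.

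Several stronger readings are tempting and are not supported:

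- **That the bias exceeds the effect the trial is sized for.** A reader might take the 52.3% reduction in the Background with an assumed baseline of 60 mm (31.4 mm) and obtain 0.20 × 2/3 × 31.4 = 4.2 mm, above 3.4 mm. That sets a medicinal-cupping result and an invented baseline against an SD that belongs to a 12.78 mm change. On the planning change the same scenario gives 1.7 mm, about half of 3.4 mm.
- **That standard errors are too small.** The check does not show this. Under equal dropout the type I error stays near 0.05; the harm is bias and lost power.
- **That the article expects unequal dropout.** The Background speaks of high dropout in conventional randomized trials and offers the preference design as the remedy. Unequal dropout is possible here, but it is an assumption, and nothing says which arm would lose more.
- **That one missed session freezes all later values.** The dropout definition and the worked example can be read together that way, but the article does not say that later assessments are discarded or not collected.
- **That satisfaction is to be imputed by LOCF or restricted to completers.** Satisfaction sits in a separate paragraph with no stated imputation. Dropout and its reasons are themselves a primary outcome, so dissatisfaction shown by leaving is not wholly hidden. What stands is that early leavers have no satisfaction score.

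**Conclusion.** The point holds for the efficacy analysis. LOCF is a poor main method for a pain score that is expected to fall over five weeks and may rise over the next twelve. On the plan's own change of 12.78 mm, an assumed 25% versus 5% dropout produces a false difference of about 1.7 to 2.6 mm, which is half to three quarters of the 3.38 mm implied by reading 0.2875 as Cohen's f. An assumed 15% loss after week 5 with full relapse overstates follow-up benefit by about 1.9 mm. Equal dropout produces no false positives beyond 5% but shrinks a true difference, so LOCF cannot be defended as conservative for the equivalence aim.

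These sizes rest on assumed dropout splits and on applying the cupping change to both arms. The missing satisfaction score for early leavers is a secondary point. The change should be made; it is moderate in weight because VAS is secondary.

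**What to change.** In the Statistical analysis section, replace carry-forward with a linear mixed model for repeated measures on all observed VAS values. Include baseline VAS, treatment, visit, treatment-by-visit, and a term for randomized versus preference participants, with no single imputation. State that outcomes continue to be collected after missed sessions where possible.

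As the sensitivity analysis, use one that departs from missing at random, for example assigning dropouts a return toward baseline of varying size, varied by arm. LOCF does not serve this purpose, because it does not test that assumption.

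For satisfaction, ask the item at the withdrawal contact where possible, and add a sensitivity analysis that places participants without a score in the worst category.

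The cost is revised analysis wording, one question at withdrawal and a little more analysis work. The main analysis would then rely on missing at random, and the sensitivity analysis is there to probe that.

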### Ethical issue

This protocol, including the informed consent document and case report form, has been approved by the Institutional Ethics Committee of Beijing University of Chinese Medicine Affiliated Dongfang Hospital (approval number: 2013052104-2). All participants will be required to sign the informed consent form. Participant names will appear as pinyin abbreviations on CRFs. Only the practitioner who will oversee enrollment and outcome assessors will be aware of participants’ personal information, which will not be shared with other researchers and practitioners.

## Discussions

The average age of onset of fibromyalgia is 45 years with morbidity increasing with age [32]. Our systematic review of randomized controlled trials on TCM treatment for fibromyalgia found that the average age of patients was 40 to 50 yrs [20]. Thus, for this trial we will include persons aged 20 to 60 years, in order to focus on this high-risk group.

Researchers of this study include professionals in epidemiology, evidence-based medicine, biostatistics, and clinicians, all of whom will ensure the quality of design, application, and evaluation of this clinical trial. All acupuncturists and cupping therapists will be screened for licensure in traditional Chinese medicine and clinical experience of at least one year.

## Trial status

This study has been in the active recruitment phase since July 2013.

## Abbreviations

BL: bladder channel; CRF: case report form; FIQR: Revised Fibromyalgia Impact Questionnaire; HAMD: Hamilton Depression Scale; PRPP: partially randomized patient preference; RCT: randomized controlled trial; SD: standard deviation; SS: symptom severity; TCM: traditional Chinese medicine; VAS: visual analogue scale; WPI: widespread pain index.
